#### Secondary

TRAb titre and related thyroid hormone status at the time of RTX administration and 2 years post-RTX.Time to recovery of B cell lymphocyte numbers in peripheral blood to the normal local lab reference range in relation to thyroid hormone status.Cumulative dose of ATD (mg/kg) in relation to thyroid hormone status 2 years post-RTX.Time taken for TSH and thyroid hormone concentrations to normalise to within the local laboratory reference range post-RTX, and describe biochemical thyroid status in the period between cessation of ATD and 2 years post-RTX in each patient.The frequency and nature of adverse events.

### Visit details and assessments

Following screening and consent, RTX is administered at the baseline visit (week 0). Subsequent visits are scheduled until 24 months; the details are provided in table 2. In addition, after each visit in the first 12 months, participants are contacted by telephone to document changes in ATD dosages. Calls should be completed within 10 days of the visit.

**Table 2 T2:** Schedule of events

Assessments/Intervention	Trial period														
	Screening/Consent	Trial intervention	Follow-up												
	Week −6 to 0	0	4	8	12	16	20	28	36	44	52	65	78	91	104
Confirmation of eligibility	X	X													
Informed consent and assent	X														
HBsAg, HB Core and HCV antibodies	X														
Pregnancy test (women)	X	X									X				
Medical history		X													
Clinical examination		X	X	X	X	X	X	X	X	X	X	X	X	X	X
Height		X						X			X		X		X
Weight		X	X	X	X	X	X	X	X	X	X	X	X	X	X
RTX infusion		X													
ATD regimen		X	X	X	X	X	X	X	X	X	X				
ATD compliance			X	X	X	X	X	X	X	X	X				
Concomitant medication		X	X	X	X	X	X	X	X	X	X	X	X	X	X
Adverse and serious adverse event		X	X	X	X	X	X	X	X	X	X	X	X	X	X
Thyroid function (TSH, FT4 and FT3)		X	X	X	X	X	X	X	X	X	X	X	X	X	X
Liver function (ALT and bilirubin) if on PTU		X	X	X	X	X	X	X	X	X	X	X	X	X	X
Thyroid antibodies (TRAB and TPO)		X			X			X	X		X				X
Lymphocyte subsets*		X	X		X			X	X		X				X
Full blood count		X	X		X			X	X		X				X
Immunoglobulin levels (IgG, IgM, IgA)		X			X			X	X		X				X
Specific antibody levels (tetanus, Hib, pneumococcus)		X									X				X
Thyroid function (TSH, FT4 and FT3)—central analysis		X									X				X
Serum for exploratory analyses		X									X				X

ATD dose is adjusted at each visit if required.

*Lymphocyte subsets: T cells (CD3), helper T cells (CD4), cytotoxic T cells (CD8), B cells (CD19) and class switch B cells (CD27+ IgD−).

ALT, alanine transaminase; ATD, antithyroid drug; FT3, free tri-iodothyronine; FT4, free thyroxine; HB Core, hepatitis ‘B’ Core antibody; HBsAg, hepatitis ‘B’ surface antigen; HCV, hepatitis ‘C’ virus antibody; Hib, haemophilus influenzae type B; PTU, propylthiouracil; RTX, rituximab; TPO, thyroid peroxidase; TRAb, thyrotropin receptor antibody; TSH, thyroid stimulating hormone.

HBsAg, HB Core antibody and HCV antibody status is checked at screening/consent to establish hepatitis status to determine if the patient can be entered into the trial. A full blood count is conducted to look for evidence of change in white cell number (a recognised side effect of ATD). Lymphocyte subsets including T cells (CD3+), helper T cells (CD4+), cytotoxic T cells (CD8+), B cells (CD19+) and class switch B cells (CD27+ IgD−) and serum immunoglobulin (Ig) levels (IgG, IgM, IgA) are measured to look at the impact of RTX (anti-B cell MAb) on B and T cell populations and immunoglobulin levels (produced by plasma cells that differentiate from B cells).

Specific vaccine antibodies (against tetanus, haemophilus influenzae type B and pneumococcus) are assessed at baseline and at 12 and 24 months to look for evidence of falling levels as a consequence of the intervention.

At each visit, concomitant medications are recorded, an adverse event check is performed and thyroid function (TSH, FT4 and FT3) is assessed.

We plan to undertake exploratory analyses of immune system function on blood samples obtained prior to the RTX infusion at baseline and then after 12 months and 24 months. This will include measurement of a range of novel factors involved in immune system activity, including B lymphocyte activating factor, a proliferating-inducing ligand and B lymphocyte chemoattractant (CXCL13). These data will be analysed separately from the main trial.

### Withdrawal

Participants have the right to withdraw from the trial at any time, including during the single infusion of RTX, without having to give a reason. The patient will still be asked to complete follow-up. Sites will need to record the amount of RTX that was administered prior to the patients’ withdrawal. Investigator sites should try to ascertain the reason for withdrawal and document this reason within the case report form and the participant’s medical notes.

As this is a single-dose administration, it is not anticipated that the investigator would withdraw a patient from treatment (the infusion would be slowed down accordingly—see the Intervention section). If the RTX infusion has to be stopped completely and cannot be recommenced, then those subjects receiving less than 100 mg RTX will be reviewed according to the protocol for safety reasons only. Should a participant withdraw from the trial, then every effort will be made to obtain follow-up data, with the permission of the patient.

Participants who withdraw from the trial will not be replaced.

### Sample size

Formal justification to proceed to a larger randomised trial is based on observing a minimum number achieving remission 2 years post-RTX administration; this number is referred to as the critical number.^42^ The critical number depends on the desired and unacceptable remission rates, set at 40% and 20%, respectively, and the error levels set at 10% alpha (type I) and 20% beta (type II). The remission rate corresponding to the critical number will lie between 40% and 20% and will be specified and stored separately in the Statistics trial master file (TMF). If the true remission rate is 40%, there is an 80% chance (power) of proceeding to a further trial; if the true remission rate is 20%, there is a small 10% (alpha) chance of proceeding to a further trial. With these parameters the target recruitment is 27 patients who will receive RTX. This is the smallest number of patients which satisfies the design criteria, assuming a 10% loss to follow-up.

### Statistical analysis

Patients will receive a single dose of RTX once they have fulfilled the inclusion and exclusion criteria. In the event that RTX is not well tolerated, only patients who were able to receive more than 100 mg of RTX will be included in the statistical analysis.

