## Methods and analysis

### Trial objectives

The primary objective is to establish whether a single 500 mg dose of RTX, when administered together with a 12-month course of ATD, is likely to result in a meaningful improvement in the proportion of young people with Graves’ hyperthyroidism entering disease remission.

The secondary objectives are to examine (1) the relationship between thyrotropin receptor antibody (TRAb) titre and thyroid hormone status (thyroid stimulating hormone [TSH], free thyroxine [FT4] and free tri-iodothyronine [FT3]) in recruited subjects at the beginning and end of the trial; (2) whether immune cellular response is related to disease outcome by examining the relationship between time to recovery of B cell numbers measured in peripheral blood to within the local normal reference range and thyroid hormone status at the end of the trial; (3) whether total dose of ATD is related to disease outcome; (4) the time taken for TSH concentrations to normalise post-RTX and to describe thyroid status, as assessed by TSH, FT4 and FT3 concentrations (normal or abnormal), in the period between cessation of ATD therapy and the end of the trial in each patient; and (5) the safety of the trial treatment regimen by determining the nature and frequency of adverse events.

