#### Analysis of secondary outcome measures

The distribution of TRAb titres will be compared between patients in and out of remission by graphical summary, numerical summary statistics (median and IQR) and a Mann-Whitney test.Time to recovery of peripheral blood B cell lymphocyte numbers (CD19+ cells) to above 70% of the patient’s pre-RTX level in relation to thyroid hormone status. This will be compared between patients in and out of remission by graphical summary, numerical summary statistics (median and IQR) and a Mann-Whitney test.Cumulative dose of ATD (CBZ) in mg/kg in relation to thyroid hormone status. This will be compared between patients in and out of remission by graphical summary, numerical summary statistics (median and IQR) and a Mann-Whitney test.We will assess the time taken for TSH concentrations to normalise (increase above 0.1mU/L) post-RTX and describe biochemical thyroid status, as assessed by TSH, FT4 and FT3 concentration, in the period between cessation of ATD therapy at the end of year 1 and the end of the trial. Specifically we will plot the time taken for TSH to normalise in individual patients and determine the proportion of time that TSH, FT4 and FT3 concentrations are within the normal reference range in the period between ATD stopping (end of year 1) and trial end (end of year 2).The frequency and nature of adverse events.

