### Safety reporting

We do not aim to collect adverse events such as minor trauma (scratches, cuts) in patients who are otherwise well. Adverse events will otherwise be classified according to whether they are:Infections (minor: self-limiting infection such as the common cold; modest: non-self-limiting where an antibiotic is prescribed but the clinical course and recovery is not related to the underlying condition and its treatment; or severe: where antibiotic therapy ± other therapy is required with the infection related to drug effects on immune function).Immune function-related such as neutropaenia.Related to the skin, for example, rashes.Related to the musculoskeletal system, such as joint pain.Related to gastrointestinal upset.Related to hepatic function.Others.

The trial will be stopped if a patient dies from an RTX treatment-related infection or if two patients experience the same SUSAR which has severe or life-threatening consequences.

According to section 4.6 of the summary of product characteristics (SmPC) (Mabthera [the product name for RTX] 100 mg and 500 mg concentrate for solution for infusion), RTX should not be administered to pregnant women. The SmPC states that ‘Rituximab should not be administered to pregnant women unless the possible benefit outweighs the potential risk’. Due to the long retention time of RTX in B cell-depleted patients, women of childbearing potential need to use effective contraceptive methods during treatment and for 12 months following RTX therapy (in line with the SmPC for RTX). If a female participant becomes pregnant within 12 months of taking the RTX drug, the details of the pregnancy need to be reported to the chief investigator, trial manager and sponsor within 24 hours of the site learning of its occurrence on the pregnancy reporting form.

If a patient or their partner (where the participant is male) becomes pregnant, within 12 months of taking RTX, the pregnancy must be reported as per the trial-specific guidance document for pregnancy reporting and followed up to completion of pregnancy.

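### As written, the 100 mg rule applies to the whole statistical analysis, so patients whose rituximab infusion is stopped at or below 100 mg drop out of the analysed adverse-event frequency

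*Protocol article*

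**What the plan says.** The opening paragraph of Statistical analysis sets the analysis population. When RTX is not well tolerated, "only patients who were able to receive more than 100 mg of RTX will be included in the statistical analysis". It does not separate efficacy from safety.

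Under the same heading, Analysis of secondary outcome measures ends its list with "The frequency and nature of adverse events" and names no separate population. Trial objectives makes this a formal aim: "the safety of the trial treatment regimen by determining the nature and frequency of adverse events".

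The Withdrawal section covers infusions that are stopped and cannot be resumed: "those subjects receiving less than 100 mg RTX will be reviewed according to the protocol for safety reasons only". For patients who withdraw, including during the infusion, it adds "The patient will still be asked to complete follow-up". It also states "Participants who withdraw from the trial will not be replaced".

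Data collection and trial-level safety rules carry no minimum dose. Visit details and assessments says "At each visit, concomitant medications are recorded, an adverse event check is performed", and Safety reporting says "The trial will be stopped if a patient dies from an RTX treatment-related infection".

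**The concern.** The exclusion is decided after treatment has begun and is triggered by poor tolerance. The Intervention section names the symptoms that halt an infusion: angioedema, low blood pressure and difficulty breathing. A patient whose infusion is abandoned early for one of these is directly informative about the safety of the regimen, yet the population sentence leaves that patient out of the adverse-event summary. The reported frequency would then be conditional on having tolerated more than 100 mg, which is part of what the safety objective sets out to learn.

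A related point affects the remission rate. Without a supportive estimate in everyone who started RTX, the reported rate describes only patients who got past the cut. The article would use that rate to justify a randomised evaluation of the regimen as a whole.

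**Working it through.** **1. The denominator.** Sample size gives unacceptable and desired remission rates of 20% and 40%, alpha 10%, power 80%, 10% loss to follow-up, and 27 patients receiving RTX. An exact binomial search for the smallest n with P(X ≥ r | n, 0.20) ≤ 0.10 and P(X ≥ r | n, 0.40) ≥ 0.80 gives n = 24 with r = 8 (alpha 0.0892, power 0.8081). Then 24/0.9 = 26.7, rounded up to 27. The plan's figure is reproduced, so 27 dosed patients is the right base. The value r = 8 is inferred, since the article keeps the critical number in the trial master file.

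**2. Who falls under the rule.** On the infusion steps in Intervention, if every step is tolerated:
- 50 mg/hour for 30 min gives 25 mg.
- 100 mg/hour for the next 30 min gives 50 mg, cumulative 75 mg.
- 150 mg/hour for 10 min gives 25 mg, cumulative 100 mg at 70 min.

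If the rate is held at 50 mg/hour throughout, 100 mg takes 100/50 = 2 hours. The rule therefore catches infusions permanently ended within roughly the first 70 to 120 minutes of running time.

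**3. Effect on the safety summary.** Let k be the number of the 27 dosed patients whose infusion is permanently stopped at 100 mg or less. The article gives no rate, so k is assumed. Read literally, the analysed frequency of such infusions is 0/(27 − k), against k/27 among all who started.

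| k (assumed) | Rule as written | All who started RTX |
|---|---|---|
| 1 | 0/26 | 1/27 = 3.7% |
| 2 | 0/25 | 2/27 = 7.4% |
| 3 | 0/24 | 3/27 = 11.1% |

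The zero is forced only for infusions ended at or below the cut. Reactions in patients who passed 100 mg stay in. Any other adverse events in the k excluded patients are also omitted.

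**4. How likely the case is to arise.** The chance of at least one such patient is 1 − (1 − p)^27 for an assumed true rate p: 24% at p = 1%, 42% at 2%, 75% at 5%, 94% at 10%.

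**5. The boundary.** Withdrawal assigns patients strictly below 100 mg to safety review. Statistical analysis admits patients strictly above 100 mg. Exactly 100 mg belongs to neither.

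**6. Effect on the remission rate of a supportive estimate.** Counting patients at or below the cut as not in remission leaves the number of remissions unchanged and enlarges the denominator. With k = 2 and no other losses, the rate is multiplied by 25/27 = 0.926.

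**The case against.** The strongest reply is that the two sections can be read together. Withdrawal keeps patients below 100 mg for safety, Statistical analysis removes them from efficacy, and nothing is lost. That is probably the intent. A reader might call the sections contradictory, but the text does not go that far: one governs follow-up and the other governs analysis, and the fault is one of scope. What remains is that the population sentence does not state the intended limit, and adverse events sit beneath it.

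A reader might also infer that these reactions vanish from the trial. They do not. Adverse events are checked at every visit, follow-up is requested after withdrawal, sites record the amount infused, and the stopping rule applies whatever dose was received. What is lost is a place in the analysed frequency. Nor do the documents show that the omitted reactions would be the most severe ones: a patient may stop by choice, and a severe reaction after 100 mg is retained.

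A safety population is commonly left to the full protocol or the SAP, neither of which is shown. Its absence would be no finding. The point here is a population rule that the article does state. A later document that defines a wider safety set would depart from this sentence.

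A minimum-exposure rule for efficacy, stated in advance, is a defensible choice in a proof-of-concept trial, and I do not object to it.

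Finally, a loss of power is tempting to infer, since withdrawals are not replaced. It does not hold up as part of this point. Power of 71.0% to 76.3% (n = 22 or 23, r = 8) requires two assumed exclusions on top of the full 10% loss, and an inferred critical number. Two exclusions alone leave n = 25, where P(X ≥ 8 | 0.40) = 84.6%. Counting non-tolerators as not in remission would also leave the chance of reaching a fixed critical number unchanged.

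**Conclusion.** The concern holds as a badly scoped rule. Read as written, patients whose infusion is permanently stopped at or below 100 mg are omitted from the analysed adverse-event frequency, and the analysed frequency of those early-stopped infusions is zero by construction. Illustratively, that is 0/25 in place of 2/27 = 7.4%, with a range of 3.7% to 11.1% for one to three such patients. The counts are assumptions; the direction and the forced zero follow from the wording alone. The gap at exactly 100 mg is plain but small.

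The article supports neither a direct contradiction between sections, nor a loss of the underlying safety data, nor a quantified loss of power. It should be corrected because safety is a stated objective and the correction is nearly free.

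**What to change.** - In Statistical analysis, confine the 100 mg exclusion to the efficacy analyses.
- State that adverse events are summarised for every patient in whom the RTX infusion was started, whatever amount was given.
- Reconcile the boundary wording in Withdrawal and Statistical analysis so that exactly 100 mg is assigned. Where the cut should lie is for the trial team and is not judged here.
- As a supportive analysis, report remission among all who started RTX, with those at or below the cut counted as not in remission, beside the planned rate.

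The cost is a few sentences in the protocol and SAP. No extra patients or visits are needed, since follow-up after withdrawal is already requested. The one downside is that the supportive remission rate may be slightly lower than the planned one.

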#### Analysis of the primary outcome measure

The number of patients in remission 2 years after RTX administration will be compared with the critical number. This is equivalent to a formal comparison of the hypotheses that the remission rate is greater than or equal to 40% as opposed to less than or equal to 20%. The primary outcome measure, remission rate, will be presented with a one-sided 90% lower bound. If this phase II trial provides evidence that the true remission rate is plausibly 40% or more, 2 years after a single dose of RTX and a 12-month course of ATD, then this will indicate a likely effect of RTX on disease outcome and justify a randomised efficacy evaluation of this adjuvant RTX regimen.

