### Trial design

This is an investigator-initiated, open-label, single-arm, single-stage, phase II trial using an A’Hern design^42^ to determine whether the proposed new treatment is likely to meet a minimum level of efficacy before comparing it with standard treatment in a randomised trial. A single-arm design has been chosen because use of a control arm would require a much larger sample size resulting in a longer, more expensive trial when the potential benefit of RTX is, as yet, unknown. The design requires specification of the smallest remission rate, which if true would clearly imply that the treatment warrants further investigation, and the largest remission rate below which we would not wish to proceed to a larger definitive trial.

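### The go/no-go rule fixes one critical count without reference to the number evaluable, so the false-go rate exceeds 10% if follow-up is better than planned

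*Protocol article*

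**What the plan says.** The trial is an "open-label, single-arm, single-stage, phase II trial" on an A'Hern design. The Sample size section explains what fixes the threshold: "The critical number depends on the desired and unacceptable remission rates, set at 40% and 20%, respectively", together with a 10% type I and a 20% type II error. The number evaluable is not among the things it is said to depend on. The section adds that the remission rate matching the critical number lies between 20% and 40% and is kept in the statistics master file; neither value is published.

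On size, the same section says "With these parameters the target recruitment is 27 patients who will receive RTX" and "This is the smallest number of patients which satisfies the design criteria, assuming a 10% loss to follow-up". On operating characteristics, it says that if the true rate is 20% "there is a small 10% (alpha) chance of proceeding to a further trial", with a matching 80% if the true rate is 40%.

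Analysis of the primary outcome measure gives the rule: "The number of patients in remission 2 years after RTX administration will be compared with the critical number". It also says "The primary outcome measure, remission rate, will be presented with a one-sided 90% lower bound".

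Two other sections let the denominator vary. Under Withdrawal, patients who leave are not replaced. Under Statistical analysis, only those who received more than 100 mg of rituximab are analysed.

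**The concern.** An exact binomial threshold belongs to one sample size. A count of 8 is stronger evidence out of 24 than out of 27. The rule sets a raw count against one number, while the number evaluable can be anything up to 27. If the number was derived for 24, better retention than planned makes the hurdle easier to clear under an ineffective regimen.

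The count is the formal justification for a randomised trial in patients aged 12 to 20, so what is at stake is the false-go rate. There is also a risk of a visible conflict in the report, with a count that says proceed beside a lower bound that does not exclude the unacceptable 20%.

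**Working it through.** **Inputs.** Unacceptable rate 0.20, desired rate 0.40, alpha 0.10, power 0.80, 27 recruited and 10% loss, all from Sample size. The test is one-sided, in line with the lower bound in the primary analysis section.

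**Reproducing 27.** For n evaluable and critical number r, let X be binomial(n, p). Then alpha = P(X ≥ r | p = 0.20) and power = P(X ≥ r | p = 0.40). The smallest n for which some r gives alpha ≤ 0.10 and power ≥ 0.80 is n = 24, and r = 8 is the only r that works there (alpha 0.0892, power 0.8081). Inflating for loss, 24/0.9 = 26.7, rounded up to 27. This matches the article, so its statement about the smallest number points to a critical number of 8.

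**Carrying 8 to other evaluable n.** The lower bound is the exact (Clopper-Pearson) one-sided 90% bound for 8 remissions.

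| Evaluable n | Alpha with 8 | Power with 8 | Lower bound for 8/n |
|---|---|---|---|
| 22 | 5.6% | 71.0% | 22.5% |
| 23 | 7.2% | 76.3% | 21.4% |
| 24 | 8.9% | 80.8% | 20.5% |
| 25 | 10.9% | 84.6% | 19.6% |
| 26 | 13.1% | 87.8% | 18.8% |
| 27 | 15.6% | 90.5% | 18.1% |

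Alpha passes 10% from n = 25, which is also where the bound falls below 20%.

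**Averaging over loss.** If each of 27 patients is lost independently of outcome with probability L, the count in remission is binomial(27, (1 − L)p). With critical number 8:

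- L = 10%: alpha = P(X ≥ 8 | 27, 0.18) = 9.8%; power = P(X ≥ 8 | 27, 0.36) = 81.2%.
- L = 5%: alpha = P(X ≥ 8 | 27, 0.19) = 12.5%.
- L = 0: alpha = P(X ≥ 8 | 27, 0.20) = 15.6%.

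The chance of more than 24 evaluable is 48% at 10% loss (0.252 + 0.174 + 0.058) and 85% at 5% loss.

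**Count against rate.** If the stored rate is 8/24 = 1/3 and is applied to the evaluable n, the thresholds at 25, 26 and 27 are 25/3 = 8.3, 26/3 = 8.7 and 27/3 = 9. All three require 9 remissions. The count reading therefore says proceed at 8/25, 8/26 and 8/27, and the rate reading says do not.

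**Indexing on evaluable n.** Taking the smallest r with exact alpha ≤ 10%:

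| Evaluable n | Critical number | Alpha | Power |
|---|---|---|---|
| 20 | 7 | 8.7% | 75.0% |
| 21 | 8 | 4.3% | 65.0% |
| 22 | 8 | 5.6% | 71.0% |
| 23 | 8 | 7.2% | 76.3% |
| 24 | 8 | 8.9% | 80.8% |
| 25 | 9 | 4.7% | 72.7% |
| 26 | 9 | 5.9% | 77.5% |
| 27 | 9 | 7.4% | 81.6% |

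At 28 (one patient over target) 9 also serves, with alpha 9.0%.

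**The case against.** The strongest case against has four parts.

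**The article never says that an integer 8 is applied at every n.** What it describes as stored is a remission rate. Read as a proportion, 8/24 gives the indexed table at 20 and at 22 to 27, differing only at 21 (7 instead of 8), and alpha stays below 10% from 22 to 27. The analysis plan, which is not shown, may also tie the threshold to n. This stands as a limit on the claim. It does not remove the ambiguity, because the primary analysis section compares a count and the two readings disagree at 25 to 27.

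**The stated errors hold on average.** With 27 treated, random 10% loss and a fixed 8, alpha is 9.8% and power 81.2%. A lost patient adds nothing to the count, so this needs no special rule for missing outcomes. It stands in full. A reader might infer that the 10% and 80% are wrong for the design as planned; they are not. The agreement does depend on the loss being about 10%.

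**Low power at 22 and 23 is not caused by fixing the number.** There 8 is already the smallest count that holds alpha. At 25 and 26 no critical number meets both targets, because the binomial is discrete. This stands, so only the excess alpha at 25 to 27 can be charged to a fixed 8.

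**Counting power failures under a critical number of 9 is speculation.** This stands too, because the stated inputs point to 8.

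**Conclusion.** The point holds as a moderate defect in the decision rule. Taken literally, the published rule lets the false-go rate rise above the stated 10% whenever more than 24 patients are evaluable, up to 15.6% with complete follow-up. At 8 remissions out of 25 to 27 it would say proceed while the planned bound still includes 20%.

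This rests on two assumptions: that the undisclosed critical number is 8, as the stated inputs imply, and that it is applied as a count without regard to n. The averaged figures also assume loss that is independent of outcome.

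A reader might go further and conclude that the sample size is wrong, or that both error rates fail at most evaluable sizes because of the rule. The documents support neither. The figure of 27 reproduces exactly, power falls short below 24 because n is smaller, and alpha is exceeded only above 24.

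**What to change.** Before outcomes are known, state in both Sample size and Analysis of the primary outcome measure that the critical number is set by the evaluable n: 7 at 20, 8 at 21 to 24, 9 at 25 to 28. Say whether the count or the stored rate governs, and define who counts as evaluable, since that selects the row. Exact alpha is then at most 10% in every row. Replace the flat 80% with power of about 71% to 82% for 22 to 27 evaluable, reaching 80% only at 24 and 27.

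No extra patients are needed, but there is a cost in power. The table does not cure the shortfall at 22, 23, 25 and 26. Averaged over random 10% loss, power drops from 81.2% to about 76%. Weighting the power in each row by the probability of that n, from 27 down to 20, gives 0.058×0.816 + 0.174×0.775 + 0.252×0.727 + 0.233×0.808 + 0.156×0.763 + 0.080×0.710 + 0.032×0.650 + 0.011×0.750 ≈ 0.76; n below 20 has a probability of about 0.004 and does not change this. If the sponsor prefers a fixed 8 for its power, the text should state how alpha depends on loss (9.8% at 10%, 12.5% at 5%, 15.6% at none) and not promise 10%.
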